### Sample size calculation

See Table 1.

**Table 1 pone.0306226.t001:** Sample size calculation.

Outcome: Emergency department attendance (a global measure of morbidity and a good predictor of mortality) Data source: Mbizvo *et al*. [20]			
**Target trial emulation phase**		**Prediction model phase**	
**Method**	# Proportions from the pilot study p1 <- 2977 / 8021 # valproate withdrawn group p2 <- 2471 / 8021 # group remaining on valproate # Set significance level and power alpha <- 0.05 power <- 0.80 # Z-values for two-tailed test z_alpha <- qnorm(1—alpha / 2) z_power <- qnorm(power) # Calculate sample size n <- ceiling((z_alpha + z_power)^2 * ((p1 * (1—p1)) + (p2 * (1—p2))) / (p1—p2)^2) # Display the result cat("Sample size needed for the target trial emulation study:", n, "\n")	**Method**	Sample size criteria from our previous work for developing a time-to-event prediction model to estimate the minimum required sample size for our model development are used [33].
**Result**	The minimum sample size in the target trial emulation study is 881.	**Assumptions**	
		**(i)**	We target an overall shrinkage factor of 0.9.
		**(ii)**	We assume the outcome rate to be 0.068, calculated using the 5,448 events that occurred out of 16,042 patients within the pilot study, with a median survival time of 5 years.
		**(iii)**	The performance of the model would achieve 15% of the maximum possible cox-snell R-squared for the given outcome rate.
		**(iv)**	We would consider 20 candidate predictor parameters within the model development process.

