We recently published a study of 8,991 men and 5,243 women aged 16–54 with epilepsy taking valproate in TriNetX [20]. This was a survival analysis assessing 5-year mortality and morbidity in those withdrawn from valproate between 01/06/2015–01/06/2018 (regardless of whether switched to another ASM), with propensity-matched comparisons to those who remained on valproate. Results suggested substantially increased risks of emergency department (ED) attendances, hospital admissions, falls, injuries, burns and new-onset depression in both men and women withdrawn from valproate [20]. However, these were aggregate data designed to scope potential trends and generate hypotheses, not to probe causal links.

To progress the field, we propose a comprehensive study examining mortality and morbidity outcomes in individuals who either continued valproate, switched to lamotrigine or levetiracetam, or discontinued valproate. Employing a novel approach known as target trial emulation [21,22], this study will replicate a hypothetical randomised-controlled trial (RCT) using person-level retrospective observational data from both TriNetX and Clinical Practice Research Datalink (CPRD, which encompasses 60m UK patients) [23]. Target trial emulation minimises confounder and selection biases in observational studies by statistically emulating randomisation at baseline (time 0) [21]. Individuals are then analysed based on the treatment strategy aligned with their data. Results are available quickly and shown to mirror those of an RCT [21]. This offers a cost-effective and immediate alternative to conducting an RCT [21]; crucial given the urgency for information on valproate withdrawal safety amidst ongoing regulatory changes [24,25]. Additionally, the emulation facilitates creation of causal prediction models [26]. These are developed using observed data alongside causal theory and assumptions to calculate predicted risk under different hypothetical treatment conditions, allowing “what if” questions to be addressed for each potential (counterfactual) outcome [26]. This facilitates actionable prevention [26].

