*Causal estimand*: Assesses impact of treatment arms 1–3 vs. 4 on outcome (per-protocol assumption as observational data limits ITT assessment) [21].

*Start and end of follow-up*. The start of follow-up (Time 0 or index date) will be defined as when valproate treatment discontinued (treatment arms 1–3) or prescription of valproate at a matched time (arm 4). For time-to-first-event analyses, the end of follow-up will be defined as when the outcome occurs, censoring (including deviation from assigned treatment or leaving the study catchment area), or 10 years. For recurrent events analyses, alongside censoring as above, the end of follow-up will be 10 years, allowing for all events to be assessed throughout follow-up.

*Statistical analysis*: mirrors target trial section.

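### Table 1's minimum of 881 is sized on a pooled withdrawal effect, so neither it nor the sufficiency statement is shown for any planned arm comparison

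*Protocol article*

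**What the plan says.** The sample size section (Table 1, target trial emulation phase) uses one binary outcome, described as "Outcome: Emergency department attendance (a global measure of morbidity and a good predictor of mortality". It takes two proportions from the pilot: "p1 <- 2977 / 8021 # valproate withdrawn group" and "p2 <- 2471 / 8021 # group remaining on valproate". The error rates are "alpha <- 0.05 power <- 0.80", with "Z-values for two-tailed test". The result is given as "The minimum sample size in the target trial emulation study is 881". The feasibility row then sets this against about 14,234 people on valproate in TriNetX, around a third of them later withdrawn, and judges that enough.

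The Introduction describes the pilot's exposed group as people withdrawn between 2015 and 2018 "regardless of whether switched to another ASM".

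The study itself has four arms: withdrawn to lamotrigine, withdrawn to levetiracetam, withdrawn with no new ASM, and continued valproate. The estimand is worded "Assesses impact of treatment arms 1–3 vs. 4 on outcome". Aim 1 names the three withdrawal strategies separately. Aim 2 is to predict which alternative has the lowest mortality and morbidity.

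**The concern.** The contrast that was sized is not one that the study plans. The pilot proportion of 37.1% is a mixture over everything that could follow withdrawal: lamotrigine, levetiracetam, any other ASM, or nothing. The planned analysis separates lamotrigine, levetiracetam and nothing new, and gives no place to other ASMs. Aim 2 makes sense only if the alternatives may differ, yet the sizing applies one average effect and gives no reason why it should hold in each arm.

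The results are intended for a national decision support tool, in its section on the patient's own risks. If a switch arm has a smaller excess than the pooled one, or few patients, a non-significant comparison with continued valproate could be read as reassurance when the study had little chance of detecting the difference.

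**Working it through.** **Inputs.** From Table 1: p1 = 2977/8021 = 0.3712; p2 = 2471/8021 = 0.3081; difference d = 0.0631; two-sided alpha 0.05; power 0.80. From the feasibility row: 14,234 in TriNetX with a third withdrawn, so 14,234/3 ≈ 4,745 withdrawn and about 9,489 continuing. The split of withdrawals across arms is not given.

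**Step 1: the plan's own figure.** The formula is n = (z₀.₉₇₅ + z₀.₈₀)² × [p1(1−p1) + p2(1−p2)] / (p1−p2)².

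n = 7.849 × (0.2334 + 0.2132) / 0.0631² = 880.7 (unrounded inputs), which rounds up to 881. The figure reproduces exactly. The formula gives the number in each of two equal groups. Read as a total over four equal arms (about 220 each), power per comparison would be about 29% even at the pooled effect.

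**Step 2: power for one arm at 881 per group.** Keep p2 = 0.3081 in the continuing arm and let the arm's excess be k × 0.0631, so its proportion is q = p2 + k × 0.0631. Then power = Φ( (q−p2) / √[q(1−q)/881 + p2(1−p2)/881] − 1.96 ). The multiples k are assumptions.

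| k | Excess (points) | Power at 881 per group | n per group for 80% |
|---|---|---|---|
| 1.25 | 7.9 | 94% | 569 |
| 1.0 | 6.3 | 80% | 881 |
| 0.8 | 5.0 | 61% | 1,366 |
| 0.75 | 4.7 | 56% | 1,551 |
| 0.5 | 3.2 | 29% | 3,451 |

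The condition for 80% power at 881 per group is therefore an excess of at least about 6.3 points in that arm.

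**Step 3: power at the sample said to be available.** The same formula is used with unequal groups: n₁ in the withdrawal arm and 9,489 continuing.

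| Assumed share of withdrawals | n₁ | k = 1.0 | k = 0.75 | k = 0.5 | Detectable at 80% power |
|---|---|---|---|---|---|
| One third | 1,582 | 99.8% | 96% | 69% | about 3.6 points |
| 10% | 474 | 79% | 56% | 29% | about 6.4 points |

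With a pooled-variance test the figures for the 10% arm are slightly higher (82%, 58%, 31%). All are crude: they ignore weighting, censoring on deviation from assigned treatment, and multiplicity. An equal three-way split also assumes that nobody withdrawn moved to another ASM, since such people belong to none of arms 1–3.

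**The case against.** The strongest reply is that 881 is a floor in a retrospective database study, not a recruitment target. Everyone eligible will be analysed. The feasibility row points to several thousand withdrawals in TriNetX, and a CPRD search found 29,332 + 15,315 = 44,647 people with epilepsy prescribed valproate. On an equal split, TriNetX alone keeps crude power at 80% down to an excess of about 3.6 points. Using the only pilot effect to hand is ordinary practice. The pilot is described as aggregate data, so arm-specific proportions may not be obtainable.

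Most of this stands. It shows that the study may well be large enough, and it rules out a claim that the study is underpowered. It does not rescue the stated justification, because adequacy per arm depends on a split that the article does not give.

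A reader might go further and infer that 80% power holds in every arm only if all three withdrawal arms share exactly the same effect, or that at least one arm must fall below the pooled excess. The documents do not support this. Unequal effects that all exceed 6.3 points would also give 80% power. The pilot pool included switches to other ASMs, so it is not an average of arms 1–3 alone, and all three could lie above it. Nor does the protocol claim 80% power in each arm; it states one study minimum.

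The concern cannot be set aside as detail left to a fuller plan. The article prints the sizing code, its inputs, its result and a conclusion on sufficiency, and the point is about what those fix.

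**Conclusion.** The point holds in this form: 881 is correctly computed, but per group and for pooled withdrawal v continuation, which is not a planned contrast. Neither the minimum nor the sufficiency conclusion is therefore shown for lamotrigine, levetiracetam or no new ASM against continued valproate.

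The consequence ranges from none to substantial. It is none if each arm's excess is 6.3 points or more and each arm has at least 881 patients, or if arms are large enough to detect smaller effects. It is substantial if an arm is small or its excess is well below the pooled one. The documents cannot place the study in that range, since they give neither arm-specific effects nor arm sizes. The calculations rest on assumed multiples and shares, a continuing-arm risk of 30.8%, and the feasibility row's numbers taken at face value. This is an unsupported effect-size assumption in a stated design figure, not an arithmetic error.

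**What to change.** In Table 1, restate 881 as the number per group for 80% power to detect the pilot's pooled withdrawal v continuation difference in ED attendance, and say that it does not apply to the separate arms. Base the sufficiency statement on projected numbers in each of arms 1–3 and in arm 4, leaving out people switched to other ASMs. For each of the three comparisons, give the smallest difference detectable with 80% power, ideally with an allowance for weighting and censoring.

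If the pilot can be split by what was started, compute the requirement for each arm from its own ED proportion and state the largest as the minimum. If the aggregate data do not allow that, the detectable differences are enough.

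Relabelling and the detectable differences cost a short edit and a feasibility count of arm sizes. Design, cohort and data extraction are unchanged. The downside is that the stated figure may look less favourable for some arms.

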		**Outcome based these assumptions**	
			The minimum sample size for model development is 1,204 observations.
**Feasibility**	The TriNetX sample, derived from the pilot study, captures approximately 14,234 people with epilepsy prescribed valproate between 2015–2018, with around a third subsequently withdrawn. This is sufficient. We have also undertaken a CPRD feasibility search, identifying 29,332 men and 15,315 women with epilepsy prescribed valproate in between 2010–2021, which should also generate sufficient numbers.		

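### Table 1 gives 881 as the minimum for the whole emulation, but its formula returns 881 per group for one equal-sized two-group comparison, and adequacy is not checked for each withdrawal arm

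*Protocol article*

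**What the plan says.** The emulation column of Table 1 (Protocol article, Sample size calculation) prints R code for emergency department attendance treated as a proportion. The inputs are "p1 <- 2977 / 8021 # valproate withdrawn group" and "p2 <- 2471 / 8021 # group remaining on valproate", with "alpha <- 0.05 power <- 0.80" and the comment "Z-values for two-tailed test". The Result row reads "The minimum sample size in the target trial emulation study is 881", and the code's own output label likewise attaches the number to the study. Nothing in the table says that it is per group.

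The Treatment arms list has four entries: withdrawn and started on lamotrigine, withdrawn and started on levetiracetam, withdrawn with no new antiseizure medication (ASM), and continuing valproate. The causal estimand is described thus: "Assesses impact of treatment arms 1–3 vs. 4 on outcome". The pilot that supplies the two proportions defined withdrawal "regardless of whether switched to another ASM" (Introduction).

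The Feasibility row cites about 14,234 people in TriNetX, around a third of them later withdrawn, and concludes "This is sufficient". It also cites 29,332 men and 15,315 women in CPRD.

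**The concern.** A formula with the sum of the two group variances over the squared difference gives the number for one group. Reported as the number for the study, it understates the requirement by a factor of two for the contrast it describes, and it takes no account of a design with three withdrawal arms.

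The label matters because 881 is the yardstick for the claim of sufficiency. It could also be used to judge a single database if the other proves limited, which the Contingency planning section allows for. This is a safety study whose Aim 1 figures are intended for a patient decision tool. A null result from a sample accepted against too low a minimum could be read as reassurance.

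**Working it through.** **Inputs, all from Table 1.** p1 = 2977/8021 = 0.37115; p2 = 2471/8021 = 0.30807; difference d = 0.06308; two-sided α = 0.05, z = 1.95996; power 0.80, z = 0.84162. Variances: p1(1−p1) = 0.23340 and p2(1−p2) = 0.21316, sum 0.44656.

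**Reproducing the plan's figure.**

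n = (1.95996 + 0.84162)² × 0.44656 / 0.06308² = 7.84888 × 0.44656 / 0.0039796 = 880.73, rounded up to 881.

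The match is exact.

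**Is this a total or a group size?** Power = Φ(d/SE − 1.95996), with SE² = 0.23340/n1 + 0.21316/n2.

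| n1 (withdrawn) | n2 (continuing) | Meaning | Power |
|---|---|---|---|
| 881 | 881 | 881 in each group | 80.0% |
| 440.5 | 440.5 | 881 in total, two equal groups | 50.9% |
| 220.25 | 220.25 | 881 in total, four equal arms, one contrast | 28.8% |
| 293.7 | 587.3 | 881 in total, one third withdrawn, pooled | 45.8% |
| 97.9 | 587.3 | 881 in total, withdrawn third split evenly, one contrast | 22.5% |

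So 881 is the group size. The total is 2 × 881 = 1,762 for one contrast and 4 × 881 = 3,524 for four equal arms. Unequal allocation cannot rescue 881 as a total. The smallest total that gives 80% power for one contrast, with groups in proportion to their standard deviations, is 7.84888 × (√0.23340 + √0.21316)² / 0.0039796, or about 1,761.

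**Minimum under the allocation that the Feasibility row implies.** One third of 14,234 is about 4,745 withdrawn, leaving about 9,489 continuing. Solving for the withdrawal arm m against 9,489:

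m = 0.23340 / (0.0039796/7.84888 − 0.21316/9,489) = 0.23340 / (0.00050703 − 0.00002246) = 481.7, so about 482.

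That is 482/4,745 = 10.2% of the withdrawn, before any loss of precision from weighting.

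**Would the pool suffice?** If the 4,745 split evenly (an assumption; the split is not given), each withdrawal arm has about 1,582. Against 9,489, power per contrast is 99.8%.

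**Optional sensitivity values, on assumptions that the article does not make.**
- Bonferroni over three contrasts (α = 0.05/3): 1,175 per arm with equal groups, or about 653 per withdrawal arm against 9,489.
- A design effect of 1.3 to 2.0 from weighting, applied to both groups: about 635 to 1,010 per withdrawal arm against 9,489.
- An even split with a design effect of 2: about 93% power per contrast, or about 85% with Bonferroni as well.

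**The case against.** The arithmetic is correct; only the label is wrong. The databases are fixed and retrospective, so 881 sets no recruitment target, and nobody proposes to analyse 881 people. Continuers form a large shared comparator and weighting does not require equal groups, so a demand for 881 in every arm would impose an allocation that the plan does not have. The Feasibility row mentions the withdrawn third. It counts only 2015–2018 for TriNetX, while the study period runs from 2014 to 2024, and CPRD adds more people. Multiplicity and weighting loss can properly be left to an analysis plan.

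All of this stands. It limits the consequence but does not make the Result row true, since no allocation of 881 people reaches 80% power for even one contrast.

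One could also take the estimand to be a single pooled contrast of arms 1–3 together against arm 4. Aim 1 names the three alternatives separately, and keeping them apart is what distinguishes this study from its pilot. Even on the pooled reading, the total is 1,762.

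A reader might go further and infer that the study is underpowered, or that each withdrawal arm must hold 881 people (18.6% of the withdrawn). The documents support neither. The 881-per-arm figure assumes equal arms, and about 482 would do against 9,489 continuers. An even split would be ample.

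**Conclusion.** The stated minimum is wrong as written. The figure 881 is per group for one equal-sized comparison of all withdrawn with continuing, so the total is 1,762, twice the number printed, or 3,524 for four equal arms. Taken as a total, 881 gives about 51% power for that contrast and about 29% per contrast over four equal arms.

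Sufficiency has not been checked where it could fail, in the smallest of arms 1–3. No shortfall is shown either.

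These figures rest on three assumptions:
- The pilot's pooled difference of 6.3 percentage points applies to each withdrawal arm, although the pilot did not separate switchers from non-switchers.
- The one-third withdrawal figure holds. The 4,745 is also an upper bound for arms 1–3 combined within that pool, because people switched to some other ASM belong to none of them.
- Weighting costs no precision.

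**What to change.** In Table 1, do one of the following:
- Restate the result as 881 per group for an equal-sized two-group comparison (1,762 in total; 3,524 if four equal arms), two-sided 5%, 80% power.
- Give the minimum per withdrawal arm under the expected allocation: about 482 against about 9,489 continuing, before any loss from weighting.

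Correct the code's output label to match. State that the assumed difference comes from pooled withdrawal and may differ by arm. In the Feasibility row, replace the claim of sufficiency with the expected count in each of arms 1–3, for each database, set against that minimum. Bonferroni or design-effect values may be added as sensitivity figures if their assumptions are stated.

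The cost is a change of wording and one count query by arm. No extra patients or design changes are needed, although the stated minimum becomes less favourable.

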#### Target trial emulation using observational data from TriNetX and CPRD

*Eligibility criteria*. Anonymised, person-level, electronic health data will be extracted from TriNetX and CPRD, linked across primary care, ED, inpatients, outpatients, and mortality subsets. The study period will be from 01/01/2014 to 01/01/2024. Included will be men and women aged 16–54 years. The study will take an open cohort design with patients entering the cohort when the following criteria are met:

Either: ≥1 epilepsy disease or symptom code recorded during the study period and two separate valproate prescription instances over the preceding 12 months before at least one of the epilepsy disease or symptom codes;

Or: ≥1 epilepsy disease or symptom code recorded any time before the study period with at least two separate valproate prescription instances over 12 months during the study period.

TriNetX and CPRD use ICD-10-CM and SNOMED codes, respectively. The coding strategy combining disease and symptom codes with valproate, as used our published study successfully [20], was shown to accurately identify epilepsy cases in our prior work [28,29].

Treatment arms:

Withdrawn valproate and commenced lamotrigineWithdrawn valproate and commenced levetiracetamWithdrawn valproate and no new ASM commencedContinues valproate

*Treatment assignment*. Baseline (time 0) will be defined as when valproate dose reduction commences (treatment arms 1–3) or prescription of valproate at a matched time (arm 4). Eligible individuals are assigned at baseline to the treatment strategy that their data are consistent with [21]. To emulate randomisation, adjustment is made for baseline confounders using Robins’ generalised methods (g-methods, e.g., inverse probability weighting) [21], considering age, sex, ethnicity, deprivation, type of epilepsy (using G40 codes), baseline seizure frequency (symptom codes recorded over preceding 12 months), alcohol excess, developmental delay, Cambridge Multimorbidity Score, length of valproate treatment, valproate dose, and ASMs used other than valproate. The final set of covariates required to adjust for confounding will be chosen using a causal directed acyclic graph [21].

*Outcomes*. These are listed in the target trial design section and derived from our prior work [1,20,30,31], and public consultation. All coded events will be recorded for flexible categorical or continuous analyses, as needed.

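### Table 1's 881 is a per-group size for an unweighted 1:1 comparison, but it is stated as the whole-study minimum with no allowance for variance inflation from the planned confounder adjustment

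*Protocol article*

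**What the plan says.** The target trial emulation column of Table 1 (Protocol article, Sample size calculation) takes two emergency department attendance proportions from the pilot study: "p1 <- 2977 / 8021 # valproate withdrawn group" and "p2 <- 2471 / 8021 # group remaining on valproate". It fixes two-sided 5% significance and 80% power ("Set significance level and power alpha <- 0.05 power <- 0.80"; "Z-values for two-tailed test") and applies the standard two-proportion formula, "n <- ceiling((z_alpha + z_power)^2 * ((p1 * (1—p1)) + (p2 * (1—p2))) / (p1—p2)^2". The Result row reads: "The minimum sample size in the target trial emulation study is 881".

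The Feasibility row sets this against about 14,234 TriNetX patients, about a third of them withdrawn from valproate, and against 29,332 men and 15,315 women in CPRD. It calls the TriNetX number sufficient and expects the CPRD number to be so. It gives no count for any single withdrawal arm.

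The analysis is described under the section on emulation with TriNetX and CPRD data. There are four arms. To stand in for randomisation, "adjustment is made for baseline confounders using Robins’ generalised methods (g-methods, e.g., inverse probability weighting". A list of candidate covariates follows, and the final set is to be chosen with a causal graph. The causal estimand compares arms 1, 2 and 3 with arm 4, and follow-up is censored at deviation from the assigned treatment.

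**The concern.** The stated minimum does not match the comparison it is meant to support, in two ways.

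First, the formula gives the number in each group. The Result row presents that number as the minimum for the study.

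Second, the formula's variance term is that of two groups of equally weighted, exchangeable patients. Weighting to balance covariates gives patients unequal weights. As a rule of thumb, the effective size of an arm is then n/(1 + CV²), where CV is the coefficient of variation of the weights. Because 881 per group sits exactly at 80%, any net inflation above 1 takes an 881 versus 881 comparison below the stated power.

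The pilot does not close this gap. According to the Introduction, its comparisons were propensity-matched, so the effect size is already adjusted, but that says nothing about the variance of a weighted four-arm analysis. At stake is whether the Feasibility row tests the right number, above all for the smallest switch arm.

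**Working it through.** **Inputs from Table 1.** p1 = 2977/8021 = 0.37115; p2 = 2471/8021 = 0.30807; difference δ = 0.06308. Two-sided α = 0.05, power 0.80, so (1.960 + 0.842)² = 7.849.

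**Input derived from the Feasibility row.** About a third of 14,234 withdrawn gives 4,745 withdrawn and 9,489 continuing.

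**Assumption.** D is the net variance inflation, the same in both arms. The documents give no value, so a range is shown.

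**1. Reproduce the plan's figure.** v1 = p1(1 − p1) = 0.23340; v2 = p2(1 − p2) = 0.21316; sum 0.44656.
n = 7.849 × 0.44656 / 0.06308² = 880.7, rounded up to 881. This matches Table 1 and is the number per group, so two groups need 2 × 881 = 1,762.

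**2. Power of 881 under each reading, no weighting.** Power = Φ(δ/SE − 1.960), with SE² = v1/n1 + v2/n2.
- 881 in each group: SE = 0.02251, δ/SE = 2.802, power 80.0%.
- 881 in total, split 1:1 (440.5 each): SE = 0.03184, δ/SE = 1.981, power 51%.

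**3. Add the inflation.** Replace each n by n/D.

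| D (assumed) | 881 vs 881: power | Per arm for 80% at 1:1 (881 × D) | 881 vs 9,489: power | Switch-arm patients for 80% vs 9,489 |
|---|---|---|---|---|
| 1 | 80% | 881 | 96% | 482 |
| 1.25 | 71% | 1,102 | 91% | 610 |
| 1.5 | 63% | 1,322 | 86% | 740 |
| 2 | 51% | 1,762 | 75% | 1,011 |

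The last column solves the same formula for the switch arm: n1 = D·v1 / (δ²/7.849 − D·v2/9,489). At D = 1.5 this is 0.35010 / (0.00050703 − 0.00003370) = 739.6, so 740.

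**4. Where the minimum could bind.** As shares of the 4,745 withdrawn, the switch-arm requirement is 482/4,745 = 10% at D = 1 and 1,011/4,745 = 21% at D = 2. An arm holding between 10% and 21% of those withdrawn could pass or fail depending on the factor Table 1 leaves out. If those withdrawn split evenly (assumed; 1,582 per arm), power at D = 2 is 93%, and 80% is kept up to D of about 3.0.

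None of these figures allows for information lost through censoring at treatment deviation.

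**The case against.** Four points count on the other side.

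- **Weighting is not fixed.** It is given only as an example of a g-method, and the covariates listed are candidates. No weight distribution is stated, so every D above is assumed. The n/(1 + CV²) approximation can also overstate the loss, because estimated weights or outcome adjustment may recover precision. This stands: the shortfall is conditional and cannot be derived from the documents.
- **881 is a floor.** No recruitment target depends on it, and the expected numbers are far larger. A reader might infer from the 51% to 71% range that the study is underpowered. The documents do not support that, because those figures require the continuing arm to be cut to 881, whereas the Feasibility row implies about 9,489. All withdrawn patients together (4,745) against 9,489 keep 80% power up to D of about 7.1.
- **The arithmetic is right.** This also stands: 881 follows from the printed formula. The faults are the label on the result and the choice of an unadjusted variance.
- **Weight diagnostics usually belong in an analysis plan**, which is not shown. Their absence is not a fault. The stated minimum, however, is printed in this article and is misdescribed there.

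**Conclusion.** The point holds in a limited form. Without any assumption, 881 is a per-group number reported as the size of the whole study; two groups need 1,762, and 881 in total at 1:1 would give 51% power. Under an assumed D of 1.25 to 2, 881 per arm at 1:1 gives about 71% down to 51%, because the calculation has no slack and no term for adjustment.

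The consequence is confined to the stated minimum and its feasibility check. At the numbers in the Feasibility row, 881 switchers keep 91% to 75% power over the same range of D. A single small switch arm could still miss its requirement, and the plan gives no arm counts by which to tell. These results take the pilot proportions and the Feasibility row at face value, use the same D in both arms, and ignore censoring.

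It would also be too strict to conclude that every arm must reach an effective size of 881. Against about 9,489 continuers with the same D, roughly 490 to 505 effective switchers suffice (740/1.5 = 493; 1,011/2 = 505).

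**What to change.** - Relabel 881 in the Result row as the number per compared arm, 1,762 for two groups, before any weighting.
- State an assumed range for D and restate the minimum over it: about 1,102 to 1,762 per arm at 1:1 for D from 1.25 to 2, or, under the allocation implied by the Feasibility row, about 610 to 1,011 in the switch arm against 9,489 continuers.
- Apply the Feasibility check separately to arms 1, 2 and 3 against arm 4, using expected arm counts.
- If weighting is used, report each arm's effective sample size, (Σw)²/Σw², and judge each contrast by the power implied by both arms' effective sizes.

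The cost is a restated figure, three feasibility checks and one diagnostic; no further patients are needed. The downside is a less favourable stated minimum, which the smallest switch arm may miss. The section on study status says data access was still being sought, so the change can precede analysis.

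### Table 1 gives every pilot patient five years at risk and mislabels that five years as median survival; the first-event rate of 0.068 is too low and the minimum of 1,204 slightly low

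*Protocol article*

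**What the plan says.** The prediction-model column of Table 1 (Sample size calculation) lists four assumptions:

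- (i) The target for overall shrinkage is 0.9.
- (ii) The event rate is stated thus: "We assume the outcome rate to be 0.068, calculated using the 5,448 events that occurred out of 16,042 patients within the pilot study". The time that belongs to this rate is described in the same sentence by the phrase "with a median survival time of 5 years".
- (iii) The anticipated Cox-Snell R-squared is set at 15% of its maximum at that rate.
- (iv) The number of candidate parameters is 20.

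The result is given as: "The minimum sample size for model development is 1,204 observations".

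The counts in (ii) are those of the target-trial column of the same table, "p1 <- 2977 / 8021 # valproate withdrawn group" and "p2 <- 2471 / 8021 # group remaining on valproate", added together. Three other places bear on the point. The Introduction describes the pilot as a survival analysis with a five-year horizon. The section on Aim 2 specifies a Cox model for time to first event. The paragraph on start and end of follow-up ends first-event follow-up when the outcome occurs.

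**The concern.** A rate for a time-to-first-event model is the number of first events divided by the time patients spent at risk of a first event. Time after the event does not count. Multiplying the number of patients by five puts that time into the denominator, so the rate comes out too low.

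The wording adds a second difficulty. Read literally, a median survival time of five years means that half the patients have had the event by then. The table's own counts give about a third. A reader who tries to rebuild the calculation from the words will not get the published number.

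At stake is the accuracy of a stated planning figure. The rate and the follow-up time together set the maximum Cox-Snell R-squared, and through it the minimum sample size for model development.

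**Working it through.** **Inputs (Table 1).** Events 2,977 + 2,471 = 5,448; patients 8,021 + 8,021 = 16,042; time 5 years; shrinkage S = 0.9; anticipated R² = 15% of its maximum; P = 20 parameters. The counts are taken as stated.

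**1. Where 0.068 comes from.**
5,448/16,042 = 0.3396, and 0.3396/5 = 0.0679, which rounds to 0.068.

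**2. Reproducing 1,204.** The shrinkage criterion for a time-to-event prediction model, with an exponential null likelihood and E events per person, is

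- max R² = 1 − exp{2(E ln(rate) − E)}
- n = P / [(S − 1) ln(1 − R²/S)]

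With rate 0.068 and 5 years for everyone, E = 0.34. Then max R² = 0.9186, R² = 0.15 × 0.9186 = 0.1378 and n = 1,203.6, rounded up to 1,204. This is the stated figure, so the table did use 0.068 with 5 as each patient's follow-up time. Two alternative forms of the calculation do not match: 1,484 with ln(E) in place of ln(rate), and 1,560 with the binary-outcome version.

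**3. Is 0.068 a first-event rate?** At a constant 0.068, the five-year risk is 1 − exp(−0.34) = 28.8%, not the 34.0% it was derived from. The constant hazard that gives 34.0% by five years is −ln(1 − 0.3396)/5 = 0.083 per year, with mean time at risk 0.3396/0.083 = 4.09 years. The stated rate is about 18% lower (0.068/0.083 = 0.82). Placing events at mid-interval instead of assuming a constant hazard gives 0.082.

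**4. Does the five-year median fit?** With complete follow-up, 34.0% with an event by five years leaves 66% event-free, so the median event-free time lies beyond five years. At a constant 0.068 it would be ln 2/0.068 = 10.2 years. A five-year median needs ln 2/5 = 0.139 per year, about twice the stated rate.

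**5. Effect on the minimum.** The pilot person-years are not in the document, so the mean time at risk m is varied as an assumption. The pilot's 34.0% is held fixed (E = 0.3396, rate = 0.3396/m).

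| Mean time at risk (years) | Rate per year | Max R² | Minimum n |
|---|---|---|---|
| 5 (as in Table 1) | 0.068 | 0.918 | 1,204 |
| 4.5 | 0.075 | 0.912 | 1,213 |
| 4.09 (constant hazard, complete follow-up) | 0.083 | 0.907 | 1,222 |
| 3 | 0.113 | 0.885 | 1,254 |
| 2 | 0.170 | 0.848 | 1,313 |

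Relative to 1,204 these are +0.7%, +1.5%, +4.2% and +9.1%.

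**The case against.** The best defence is that the 5 was never meant as the time by which half have the event. If follow-up was complete to five years and 34% had an event, the other 66% were each observed for five years. The median observed time is then exactly five years. On that reading the count, the time and a crude rate can stand together as loosely worded summaries. This part stands: the 5 works as follow-up, and the label is a slip of wording. It does not rescue the rate, which needs total (equivalently mean) time at risk. Within a five-year horizon the mean must be below five years once anyone has an event.

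A second objection is that the direction of the correction is open. Putting in 0.083 and keeping five years for everyone gives 1,168, and a literal five-year median gives 1,117 to 1,162; all are below 1,204. But 0.083 × 5 implies 0.415 events per person, and the literal median implies at least 50% with an event. Neither agrees with the pilot's 34.0%. With that proportion held fixed, every mean time at risk below five years raises the minimum.

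Two further objections stand. The sample-size formula was applied correctly to the stated inputs. And without the pilot person-years no single replacement figure is established.

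**Conclusion.** The point holds as a minor correction of stated planning figures. As a first-event rate 0.068 is too low: about 0.083 per year if the hazard is constant and follow-up complete to five years, and higher if follow-up was shorter. The five years is mislabelled. The minimum of 1,204 inherits the derivation and is slightly low: about 1,222 under those two conditions, and 1,213 to 1,313 over the assumed range of mean time at risk from 4.5 down to 2 years.

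A reader might infer that the study is undersized or that its sample-size calculation is invalid. The documents do not support either. The 1,204 follows exactly from the inputs given, the change is small, and the feasibility row of Table 1 reports about 14,234 people in TriNetX, more than ten times the largest figure above. Nor should 1,222 be treated as the established answer, since it depends on the constant-hazard and complete-follow-up assumptions.

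The conclusion takes the event and patient counts as printed and treats them as first events within the pilot's five-year horizon.

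**What to change.** In assumption (ii) of Table 1:

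- Replace 0.068 by first events divided by the actual person-years at risk in the pilot, and give the unit.
- Relabel the five years as the follow-up used, and state the mean time at risk beside it.
- Recompute the minimum from those inputs.

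If the pilot person-years cannot be obtained, state the constant-hazard and complete-follow-up assumptions with 0.083 and 1,222, and show the range 1,213 to 1,313.

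The cost is two figures and one phrase in the table, plus looking up the pilot person-years. The restated minimum will be slightly higher; recruitment of data, design and analysis stay as they are.
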